### 5.2 Laboratory tests

No laboratory tests planned.

### 5.3 Other investigations

No other investigations planned.

# Assessment of efficacy

As this is a pure observational study without any intervention component, therefore no assessment of efficacy of the study concept itself is planned. The implementation of geriatric-surgical co-management on the traumatology ward is linked to the ‘zorgstrategisch project 2021-2024’ in UZL and is not part of this, pre-post observational study.

# Assessment of Safety

### 7.1 Specification, timing and recording of safety parameters

Precautions regarding data protections will be taken as described in section ***12 data handling and management****.* Due to the nature and design of the study (pure observational study) no other safety issues are applicable.

### 7.2 Procedures for recording and reporting adverse events (AE)

Not applicable.

### **7.3 Treatment stopping rules**

Due to the nature and design of the study, there are no stopping rules defined. All treatments are per standard of care and no investigational device or additional medication or intervention is applied during the study.

# Statistics

### 8.1 Sample size

Pre- and post-cohort: Sample size calculation was performed based on difference in the risk of complications. In literature a wide variation in complications rates have been reported ranging from 19.9% to 57% in geriatric co-management and from 55% to 71% in the usual care group ^16-18^. Hence, assuming an absolute reduction by 20%, (alfa:= 0.05, power = 0.8, two sided t-test), equal treatment groups and an expected loss of patients of about 5%; a total of 108 patients are needed per group.

Feasibility study: A total of 15 patients receiving the G-COMAN intervention will be recruited for the feasibility study. Approximately 30 healthcare professionals will be recruited for the focus groups and interviews. The total sample of healthcare professionals will be based on the willingness to participate.

### 8.2 Analysis

Pre- and post-cohort: Categorical data will be expressed as numbers and percentages. Continuous data will be expressed as means with standard deviations. Baseline characteristics will be described and compared between usual care and intervention group to evaluate the baseline equivalence. If equivalent we will test the absolute difference for our primary outcome ‘in-hospital complications’ between the two groups (t-test). If not equivalent, we will test the mean number of in-hospital complications in both groups.

Non-parametric tests will be used to compare baseline characteristics between patients who are losted to follow-up from the control and intervention group. A missing data analysis (multiple imputation) will be performed for baseline characteristics.

In addition, univariable and multivariable regression models will be used whereby the outcome will be the number of in-hospital complications. Following baseline characteristics will be used to control for potential baseline confounding: age, gender, functional status pre-fracture (Katz ADL), physical performance (Parker Mobility score pre-fracture, grip strength), cognitive status (Mini-Cog), multimorbidity (Charlson Comorbidity Index) and nutritional status (Mini Nutritional Assessment).

Secondary analyses will consist of univariable statistical tests (chi^2^ or Fisher’s exact test for categorical variables; t-test or Wilcoxon rank-sum test for continuous variables) to evaluate differences between the two treatment groups. Logistic regression will be used for dichotomous outcomes, survival analyses for time to event variables (with mortality defined as a competing risk for the outcome readmission), and ANCOVA for mean inter-group differences

Longitudinal data will be analyzed by means of mixed effects regression models to estimate differences in mean scores (eg. EQ-5D, modified Barthel Index, Parker Mobility Score, Lawton and Brody Scale) between follow-up and the respective baseline assessment by treatment group. Statistical significance is established at p-value < 0.05.

Enrolled patients who withdraw from the study follow-up for any reason (withdrawal of consent, death, loss of follow-up, …) will be included in the analyses until time at which they withdrew.

Feasibility study: Analysis of the feasibility/process indicators will be reported as frequencies and proportions for categorical data and as mean and standard deviation for continuous data. Qualitative data (focus groups and interviews) will be analysed using a thematic analysis. Two researchers will independently code the data using Word-documents. Integration of quantitative data and qualitative data will occur via embedding by linking data collection and analysis at multiple points.

We are aware of following risk of bias: lack of randomization might induce bias due to the influence of uncontrolled or unbalanced variables. Risk of bias due to death, loss of follow-up or uncompliant patients unable to complete questionnaires is possible. In the latter case, caretakers might help complete the questionnaires if feasible.

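### The only stated attrition check compares lost controls with lost intervention patients, so it nearly misses the same kind of patient being lost at different rates in the two cohorts

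*Protocol*

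**What the plan says.** Section 8.2 of the protocol fixes the contrast: "Non-parametric tests will be used to compare baseline characteristics between patients who are losted to follow-up from the control and intervention group". No section plans a comparison of lost with retained patients, or of the retained patients between cohorts.

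Four other provisions of 8.2 bear on the point:

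- Baseline characteristics are compared between the usual care and intervention groups, with no restriction to patients who remain.
- Multiple imputation is planned for baseline characteristics only.
- Patients who leave are analysed up to the time they left.
- The list of adjustment covariates is attached to the regression on the number of in-hospital complications. The mixed models for longitudinal scores have no such list.

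The section also acknowledges the risk: "Risk of bias due to death, loss of follow-up or uncompliant patients unable to complete questionnaires is possible". The only figure for loss is in section 8.1: "an expected loss of patients of about 5%; a total of 108 patients are needed per group".

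Sections 3.4, 3.6 and 5.1 show that the pre-cohort is partly retrospective. For that part, EQ-5D is not available at all. Function and nutrition are available only at baseline, and living situation and falls only at baseline and discharge.

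**The concern.** Loss to follow-up distorts a comparison between cohorts when the patients who remain no longer match. That depends on two things: who is lost relative to who stays, and how many are lost in each cohort. The planned test looks only at the lost patients and asks whether they look alike in the two cohorts. The answer can be yes while the frailest patients leave both cohorts and one cohort loses many more of them.

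At stake are the outcomes collected by post or telephone after discharge: EQ-5D, functional scales, nutrition, falls and living situation. If the post-cohort lost more of its frail patients, its remaining patients would look fitter for reasons unrelated to co-management, and the stated check would seldom show it.

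**Working it through.** **The plan's own figure.** Inputs from section 8.1: a 20-point absolute reduction, two-sided alpha 0.05, power 0.80, equal groups, usual-care risk "from 55% to 71% in the usual care group", 5% loss. No single base rate is fixed. Taking 71% v 51% (mean 0.61):

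- n = [1.96·√(2·0.61·0.39) + 0.8416·√(0.71·0.29 + 0.51·0.49)]² / 0.20² = (1.352 + 0.568)² / 0.04 ≈ 92.2, rounded up to 93.
- With continuity correction: (92.2/4)·[1 + √(1 + 4/(92.2·0.20))]² ≈ 102.
- With 5% loss: 102/0.95 = 107.4, rounded up to 108.

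The stated 108 is therefore reproducible at the top of the quoted range, and it is not in dispute here. It gives the expected number lost: 0.05 × 108 = 5.4, about 5 per group.

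**Simulation 1: same selection in both cohorts.** Setup: 108 per cohort, frailty a standard normal score, log-odds of loss rising by 1 per SD, Mann-Whitney test at 0.05. The loss model and all loss rates above 5% are assumptions. Ranges cover repeated runs.

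| Loss, pre v post | Planned test flags | Lost v retained (post-cohort) flags | Baseline gap between retained cohorts |
|---|---|---|---|
| 5% v 5% | 4% | 53-54% | about 0.00 SD |
| 5% v 20% | 6-7% | 93-96% | 0.12-0.13 SD |
| 10% v 30% | 9-10% | 97-98% | 0.15-0.16 SD |

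With the same selection and unequal rates, the planned test stays close to its 5% false-positive rate while the retained cohorts drift apart.

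**Simulation 2: selection that differs between cohorts.** Same model, 20% lost from each cohort:

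- Selection in one cohort only: the planned test flags 59-61%, gap 0.17 SD.
- Opposite selection: it flags 99% or more, gap 0.34 SD.

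The planned test does work in these cases.

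**Simulation 3: how many are lost.** Here lost patients are shifted by a fixed amount from retained ones.

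- Lost patients shifted by 1 SD in one cohort only: the planned test rejects in 20% of runs at 5% loss (5 per group), 58% at 10% (11 per group) and 89% at 20% (22 per group).
- Shifted by 1 SD in both cohorts: 3% at 5% loss, about 5% at 10% to 30%.
- Shifted by +1 and -1 SD: 67% at 5% loss and 99% at 10%. A lost v retained test pooling both cohorts rejects in only 1-2% of these runs.
- A 0.5 SD difference between lost controls and lost intervention patients: power 7-8% at 5 per group, 19% at 11, 35% at 22 and 48-50% at 32.

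The last two results matter for the remedy. Lost v retained should be examined within each cohort rather than pooled, and it should sit beside the planned comparison rather than replace it.

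**From baseline gap to outcome.** If the outcome correlates 0.6 with baseline frailty (assumed), the unadjusted bias is about 0.6 × gap: 0.6 × 0.12 = 0.07 SD and 0.6 × 0.16 = 0.10 SD. If loss depends only on that baseline score and the model adjusts for it, the bias is about zero.

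**The case against.** A reader might infer that the check cannot detect selective loss at all. It can. Selection that differs between cohorts produced the larger gaps (0.17 and 0.34 SD), and the planned test flags most of those trials at 20% loss. That part of the defence stands, and it is why the comparison should be kept. Its signal would still be mixed with baseline differences between two non-randomised cohorts.

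A reader might also infer that a null result will be presented as evidence of no attrition bias. The protocol attaches no conclusion to the test and names attrition as a possible bias, so this is not supported.

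Other fair points against the concern:

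- With equal 5% loss and equal selection, the retained cohorts do not drift apart, although a lost v retained test would still flag about half of trials. Such a flag does not itself show a distorted comparison.
- A large difference in loss, such as 5% v 20%, would be visible from counts. The protocol does not, however, commit to reporting loss by cohort and time point.
- The 5% belongs to the sample size for in-hospital complications. It does not forecast questionnaire non-response, so about 5 per group is indicative only. The number of controls at risk is also below 108, because retrospective patients have no post-discharge questionnaires.
- Models that use the baseline score remove much of the bias when loss depends on that score. They do not cover loss driven by other baseline features, such as cognition or comorbidity, that the mixed models are not said to include.
- Fuller attrition diagnostics may be in an analysis plan not shown. The protocol nevertheless states this one contrast itself, and the contrast has a blind spot.

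**Conclusion.** The concern holds in a limited form. The stated check answers a relevant question, but it nearly misses the same type of patient being lost at different rates. Under the assumed 5% v 20% loss and log-odds of 1 per SD, it flags about 6% of trials while the retained cohorts differ by about 0.13 SD. At the protocol's own 5% it rests on about 5 patients per group, possibly fewer controls, so a null result says little.

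The gap is modest, and its size rests on assumed loss rates, an assumed loss model and, for any effect on outcomes, an assumed correlation. It would be tempting to extend the point to the main result, but the primary endpoint is measured in hospital, so post-discharge loss does not reach it. The change is worth making for the follow-up secondary outcomes.

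**What to change.** Keep the planned comparison in 8.2 and add, for example: *Among patients for whom the follow-up assessment was planned, we will report (a) the proportion lost per cohort and time point; (b) within each cohort, baseline characteristics of patients with and without each assessment; and (c) baseline characteristics of retained patients compared between cohorts. Items (b) and (c) will be given as standardised differences with 95% confidence intervals and not judged by p-values.* Restricting this to planned assessments keeps retrospective patients, whose questionnaires are absent by design, from being counted as lost.

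Also state that the longitudinal mixed models adjust for the baseline covariates that 8.2 lists for the complications regression. A fixed list is preferable to covariates picked because they proved associated with loss. One listed item, grip strength, has no scheduled measurement in sections 3.6 or 5.1, so its availability should be settled first.

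The cost is a few sentences, slightly more analysis work and a few more model covariates, with no extra patients. With about 5 lost per cohort the intervals in (b) will be wide, and they should be reported as such.

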### 3.4 Trial Design

single-centre pre-post implementation study on the traumatology ward of the University Hospitals Leuven

**Usual care (pre-cohort):** the control group receives usual care on the traumato ward. This means that the patient is cared for by a surgical resident. The interprofessional team furthermore consists of ward nurses, a physiotherapist, an occupational therapist and a social worker. No tailored geriatric protocols are available to the traumato team, except for those that are available hospital-wide for all patients (e.g. fall prevention, delirium). Geriatric expertise is available upon active request by the traumato team and includes the comprehensive evaluation of the patient by a geriatric nurse (consultation model).

Due to the design of the G-COMAN strategic project and its predefined strict timing schedule (a phased implementation with the need of a rapidly full implementation), the timeframe for inclusion of the pre-cohort is limited. At the end of the pre-cohort, the predefined sample size will not be reached. To obtain sufficient included patients in the pre-cohort, this patient cohort will be supplemented with patients of which retrospectively information will be gathered. This results in a pre-cohort that will be partly prospective and partly retrospective.

**Geriatric co-management intervention, quality-improvement project G-COMAN (post-cohort):** A dedicated traumato nurse (G-COMAN nurse) will systematically perform a frailty screening in all newly admitted older patients on the traumato ward to evaluate if they are to be included in the G-COMAN program. In eligible patients, a comprehensive geriatric assessment (CGA) will be performed by the G-COMAN nurse. Based on identified potential problems, a tailored care plan based on predefined geriatric protocols will be launched. As part of the project a geriatric specialist nurse will provide every weekday training and education of the G-COMAN nurse and other team members on the traumato ward. The implementation of automated care plans and predefined geriatric protocols will be coordinated by a G-COMAN project coordinator, as well as the organisation of focus groups and intervisions to ensure smooth and supported collaboration.

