# Trial Procedures

### 5.1 By visit

### Baseline assessment

All patients who were screened for the inclusion and exclusion criteria will be entered on the ‘Subject screening log’ (see appendix 1). **Demographical data** (gender, age, height and weight (to calculate the Body Mass Index), date of admission and living situation), American Society of Anaesthesiologists (ASA) physical status class^15^, comorbidities (age adjusted charlson comorbidity Index (ACCI) will be all collected by reviewing the patients’ medical record. **Functionality** (Parker Mobility Score, modified Barthel Index, Lawton and Brody Scale, Katz index), **quality of life** (EQ-5D), **fall history and residential status** will be assessed referring to the patient’s pre-injury status. **Mental status**, based on cognition, and **nutritional status** will be assessed with respectively Mini-cog and mini nutritional assessment. Details relative to the **injury** (side affected, fracture location, fracture classification), **surgery** (time to surgery, type of procedure), and total number and intake of relevant **medication** will be documented as well. All variables, except for the quality of life, can be retrospectively collected using the electronic patient record.

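### Section 8.2 adjusts for grip strength, which the protocol never schedules, and leaves out fracture type and ASA class, which it does collect

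*Protocol*

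**What the plan says.** Section 8.2 first describes an unadjusted comparison of the primary outcome. It then states that "univariable and multivariable regression models will be used whereby the outcome will be the number of in-hospital complications". The confounders for that model are listed by name: age, gender, pre-fracture Katz ADL, "physical performance (Parker Mobility score pre-fracture, grip strength), cognitive status (Mini-Cog"), and "multimorbidity (Charlson Comorbidity Index) and nutritional status (Mini Nutritional Assessment"). For gaps in baseline data, the section says "A missing data analysis (multiple imputation) will be performed for baseline characteristics".

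The functional measures to be taken at baseline are set out in section 5.1 (Baseline assessment): "Parker Mobility Score, modified Barthel Index, Lawton and Brody Scale, Katz index". The same paragraph lists ASA class, fracture location and fracture classification among the data to be collected, and closes with "All variables, except for the quality of life, can be retrospectively collected using the electronic patient record". In the section 3.6 flowchart, type of fracture and ASA score are taken from the record and marked as available for the retrospective pre-cohort.

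Section 4.1 admits five fracture sites: proximal femur, proximal humerus, pelvis or acetabulum, thoracic or lumbar vertebrae, and wrist. Surgery is not an inclusion criterion.

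**The concern.** This is a non-randomised before-and-after comparison, and the end of section 8.2 itself acknowledges bias from uncontrolled or unbalanced variables. The t-test on the primary outcome is unadjusted. So is the alternative for non-equivalent baselines, which compares mean numbers of complications. Only the multivariable regression deals with confounding of the primary outcome, and its covariate list contains a variable with no planned source. Someone would have to change the model after data collection, with the results within reach, which a pre-specified list is meant to prevent.

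Simply dropping grip strength leaves a second gap. The cohorts can differ in fracture mix. Section 4.3 plans prospective pre-cohort inclusion from October 2021 to March 2022 and the post-cohort from September 2022 to September 2023, so the seasons covered differ, and section 3.4 adds a retrospective supplement to the pre-cohort. Neither fracture type nor ASA class is in the model, although both are collected.

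**Working it through.** **Tracing each covariate in section 8.2 to a planned source**

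- Age, gender, Katz, Mini-Cog, Charlson index and Mini Nutritional Assessment: in the section 5.1 baseline procedures and in the section 3.6 flowchart, from the record for retrospective patients.
- Parker Mobility Score: in the section 5.1 baseline procedures and covered by the sentence on retrospective collection there. It has no row in the flowchart.
- Grip strength: absent from the endpoints (3.2, 3.3), the flowchart (3.6) and the baseline, discharge and follow-up procedures (5.1). Section 5.3 plans no other investigations. The sentence "All variables, except for the quality of life, can be retrospectively collected using the electronic patient record" refers to the variables listed in that paragraph, and grip strength is not one of them.

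**Consequence for the model**

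Planned patients: 2 x 108 = 216. Observed grip strength under the written schedule: 0 of 216. A complete-case fit would use no patients. An imputation model for grip strength would have no observed values from which to be estimated.

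Scheduling the measurement now would not repair this. The current version is Amendment 2, dated 22-04-2022, and prospective pre-cohort inclusion was planned to end in March 2022. By those dates a newly added measurement could reach only the post-cohort, so grip strength would be missing for the whole control group.

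**The plan's own figure**

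The 108 per group does not bear on this point, but it can be reproduced. Assume a control rate of 71% (the top of the range in section 8.1, which does not say which rate was used) against 51%, two-sided alpha 0.05 and power 0.80:

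- Uncorrected: [1.960 x sqrt(2 x 0.61 x 0.39) + 0.842 x sqrt(0.71 x 0.29 + 0.51 x 0.49)]^2 / 0.20^2 = 92.2.
- With continuity correction: (92.2/4) x [1 + sqrt(1 + 4/(92.2 x 0.20))]^2 = 101.9, rounded up to 102.
- With 5% loss: 102/0.95 = 107.4, rounded up to 108.

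**Omitted case-mix variables: an illustration with assumed inputs**

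The protocol gives no complication risk by fracture site and no expected mix. Assume a risk of 60% for proximal femur and 30% for other sites, and a change in the femur share between periods of 10 to 20 points. The spurious crude difference is the shift times the risk gap:

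- 0.10 x 0.30 = 3 points
- 0.15 x 0.30 = 4.5 points
- 0.20 x 0.30 = 6 points

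Against the 20-point target these are 15%, 22.5% and 30%. The figures are crude: they ignore whatever part of the difference age, Katz, Parker and the other covariates would absorb, and they are on the risk scale, whereas the model's outcome is a count.

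**The case against.** The strongest reply is that the t-test named for the primary outcome needs no covariates, that the regression is introduced as an addition, and that deleting one term makes it fittable. This is right as far as it goes: the unadjusted comparison can be run. But it is the regression that addresses confounding, so the defect is not harmless.

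A second reply is that the choice of adjustment variables is a matter of judgement, that seven other covariates remain, and that the baseline comparison would show a shift in fracture mix. This stands in part. Leaving out fracture type and ASA class contradicts nothing, and a shift could be seen. Seeing an imbalance is not adjusting for it, however.

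A reader might go further in four ways that the protocol does not support:

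- That grip strength cannot be obtained from records. The protocol does not say so; it names no source.
- That retrospective availability of the Parker score is unknown. Section 5.1 states it, and only the flowchart row is missing.
- That recorded Katz, Mini-Cog, nutritional and Parker values in retrospective patients are a selected subset, because "Geriatric expertise is available upon active request by the traumato team". That sentence concerns geriatric consultation. Nothing says these scales were recorded only at such consultations, so selective recording is possible but not shown, and imputation details may properly sit in an analysis plan.
- That ASA class is held for everyone. It is planned for every cohort, but patients managed without surgery may have none.

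**Conclusion.** The point holds in two parts of different weight. First, an internal inconsistency: section 8.2 requires a covariate that the protocol neither schedules nor sources, so the only adjusted analysis of the primary outcome cannot be fitted as specified. The figure of 0 of 216 is a reading of the written schedule, not an observed missing rate. The study diagram in section 3.5, the appendices and any separate analysis plan were not available to check. The text describes the appendices as a screening log, consent forms and a staff survey, none of which would be an expected source.

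Second, a design weakness: fracture type, known for every patient by eligibility, and ASA class, planned from the record in all cohorts, are outside the adjustment set. The protocol supports no estimate of the resulting bias. The 3 to 6 points depend wholly on assumed risks and shifts, and should be labelled as an illustration wherever they are used.

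**What to change.** In section 8.2:

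- Delete grip strength from the covariate list.
- Add fracture type (proximal femur versus other) and ASA class where recorded, and state how a missing ASA class is handled.
- Add a sensitivity analysis limited to covariates recorded in essentially all patients: age, gender, Charlson index and fracture type. ASA class is left out of this set because it may be missing without surgery.

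In section 3.6, add a row for the Parker Mobility Score so that the flowchart agrees with section 5.1. This is editorial only.

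The cost is a wording change and two more model terms. The list goes from eight covariates to nine (8 - 1 + 2) if ASA class is entered as a single term. All the variables are already to be collected. The change should be made and dated before the cohorts are compared.

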# Study Synopsis

| Title of clinical trial |  | Geriatrics and traumatology co-managing fragility fractures: effectiveness and success of implementation in a single centre setting |
| --- | --- | --- |
| Protocol Short Title/Acronym |  | G-COMAN FRACTURES |
| Sponsor name |  | UZ Leuven |
| Principal Investigator |  | [name] |
| Medical condition or disease under investigation |  | Older fragility fracture patients |
| Purpose of clinical trial |  | 1) To evaluate the effectiveness of a nurse-led geriatric-traumato co-management program using outcome indicators  2) To evaluate the feasibility of a nurse-led geriatric-traumato co-management program  2.1 To evaluate the reach and fidelity  2.2 To evaluate implementation targets 2.3 To evaluate implementation determinants  3)To evaluate the process of implementation of a nurse-led geriatric-traumato co-management program  3.1 To evaluate the reach and fidelity  3.2 To evaluate process outcomes |
| Primary objective |  | 1) Effectiveness evaluation: To determine if geriatric co-management is superior in preventing in-hospital complications |
| Secondary objective (s) |  | 1) Effectiveness evaluation: To determine if geriatric co-management is superior on following outcome indicators:  - length of stay  - unplanned readmissions within 30 and 90 days  - mortality  - functional status  - nutritional status  - quality of life  - falls and new fracture rate  - Discharge to a higher care level  - secondary fracture prevention started  - Cost-benefit of G-COMAN program  2) feasibility and process evaluation: To evaluate if geriatric co-management was successful implemented on the traumato ward:  -2.1 & 3.1: reach of the program and fidelity towards the core components of the care model  - 2.2: implementation targets  - 2.3: implementation determinants  -3.2: process outcomes:  * time to start physiotherapy  * time to start dietary advice  * use and duration of physical restraints  * use and duration of indwelling catheters (urinary tract catheter or intravenous catheter)  * Medication reconciliation at admission and discharge  * referral to geriatric day clinic  * referral to fracture liaison services |
| Trial Design |  | pre-post implementation study on the traumatology ward of the University Hospitals Leuven. |

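### Section 8.2 names confounders only beside the complications model and leads the secondary analyses with univariable tests, without saying whether the later secondary models are adjusted or which estimate is the main one

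*Protocol*

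**What the plan says.** The Study Synopsis sets the secondary effectiveness objective as "To determine if geriatric co-management is superior on following outcome indicators" and lists length of stay, unplanned readmission, mortality, functional and nutritional status, quality of life, falls and fractures, discharge to a higher care level and others.

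Section 8.2 of the protocol then takes these steps in order:

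- For the primary outcome, "univariable and multivariable regression models will be used whereby the outcome will be the number of in-hospital complications". The next sentence lists the characteristics used against baseline confounding: age, gender, Katz ADL, Parker Mobility Score and grip strength, Mini-Cog, Charlson index and Mini Nutritional Assessment (MNA).
- For the rest, "Secondary analyses will consist of univariable statistical tests": chi-square or Fisher, t-test or Wilcoxon.
- The following sentence adds logistic regression for dichotomous outcomes, survival analysis (death as a competing risk for readmission) and ANCOVA for mean differences. Mixed models follow for the longitudinal scores. No covariates are named for any of these.
- The closing paragraph on bias warns that "lack of randomization might induce bias due to the influence of uncontrolled or unbalanced variables".

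Section 3.4 describes a single-centre before-after design whose control cohort is topped up with retrospectively collected patients. Section 4.3 puts recruitment of the two cohorts in different periods: October 2021 to March 2022, and September 2022 to September 2023.

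**The concern.** Length of stay, readmission, death and discharge destination plausibly depend on age, comorbidity, cognition and pre-fracture function. Nothing in the design balances these between the cohorts. An unadjusted comparison therefore estimates the programme effect plus whatever difference in case mix exists, and the error can go either way: it can create an apparent benefit or hide a real one.

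The protocol accepts a set of variables as potential confounders for complications and gives no reason for treating other outcomes in the same patients differently. Its own wording draws a contrast: univariable and multivariable for complications, univariable for secondary analyses. With two or more methods listed per endpoint and no main estimate named, the reported secondary result could be the unadjusted one. Changing the primary analysis would not alter this, because the secondary paragraph stands on its own.

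**Working it through.** **The plan's own sample size.** Section 8.1 gives "alfa:= 0.05, power = 0.8, two sided t-test", "assuming an absolute reduction by 20" percentage points, and "equal treatment groups and an expected loss of patients of about 5" percent, leading to 108 per group. No control rate is fixed; the cited rates are "ranging from 19.9% to 57% in geriatric co-management and from 55% to 71% in the usual care group". Taking 71% against 51%:

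- n = [1.96·√(2·0.61·0.39) + 0.8416·√(0.71·0.29 + 0.51·0.49)]² / 0.20² = 92.2, so 93.
- With continuity correction, 102; then 102/0.95 = 107.4, so 108. This matches.
- As a t-test with SD 0.5: 2·(1.96 + 0.8416)²·0.25/0.04 = 98.1, so 99; then 99/0.95 = 104.2, so 105.

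The figure of 108 is reproducible. It concerns complications only and does not change with this point. It is used here only for the evaluable number: 108 × 0.95 = 102.6, about 103 per group.

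**Continuous outcome (assumed inputs).** Let the outcome correlate ρ with a prognostic score, and let the cohorts differ by s SD on that score, with no true programme effect. The protocol gives neither value; ρ = 0.3 to 0.5 and s = 0.2 to 0.3 are assumptions.

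- Bias of the unadjusted difference = ρ·s, in SD units.
- Noncentrality λ = ρ·s·√(103/2) = ρ·s·7.18.
- False rejection = Φ(−1.96 + λ) + Φ(−1.96 − λ).

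| ρ | s | Bias (SD) | λ | False rejection |
|---|---|---|---|---|
| 0.3 | 0.2 | 0.06 | 0.43 | 7.1% |
| 0.3 | 0.3 | 0.09 | 0.65 | 9.9% |
| 0.5 | 0.2 | 0.10 | 0.72 | 11.1% |
| 0.5 | 0.3 | 0.15 | 1.08 | 19.0% |

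**Binary outcome (assumed inputs).** Suppose one binary risk factor is present in 50% of one cohort and 30% to 40% of the other, with outcome odds ratio 2 to 3, risk without the factor 10% to 30%, no true effect, and 108 per group.

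- Mildest case (10%, odds ratio 2, 50% against 40%): risk with the factor is 18.2%, so the spurious difference is 0.082 × 0.10 = 0.8 points and false rejection is 5.4%.
- Largest case (30%, odds ratio 3, 50% against 30%): risk with the factor is 56.25%, so the spurious difference is 0.2625 × 0.20 = 5.25 points and false rejection is 12.3%.

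**Are the covariates available?** Section 5.1 (baseline assessment) says every baseline variable except quality of life can be taken from the record for retrospective patients. Age, gender, Katz, Parker, Mini-Cog, Charlson and MNA all appear there. Grip strength is in the 8.2 list but in no assessment schedule. Section 8.2 already plans multiple imputation for baseline characteristics.

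**Limit of the illustration.** By the flowchart in 3.6, retrospective controls supply length of stay, readmission, mortality and living situation at discharge, but no follow-up function, nutrition or quality of life. The 103 per group therefore suits the first set. For the second set the control number is smaller and not stated. The bias ρ·s is the same there, but false rejection sits nearer 5%.

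**The case against.** The strongest reply is that 8.2 does not stop at univariable tests. Logistic regression, competing-risk survival analysis, ANCOVA and mixed models all follow, and each can carry covariates. ANCOVA does so by definition, and logistic regression adds little to a chi-square test unless covariates are intended. The sentence introducing the confounder list is not expressly confined to complications; only its position suggests so. Covariate lists for secondary models are also commonly left to a statistical analysis plan, which is not at hand.

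Much of this stands. A reader might infer that the secondary endpoints are tested by univariable tests alone and that case-mix differences enter the results in full. The text does not establish that; it leaves the adjustment open. Nor does the synopsis claim superiority on these endpoints: it states an objective to find out.

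Two things survive. The opening statement for the secondary analyses is a stated choice of method, so an analysis plan that made adjusted estimates the main result would depart from it. And naming models that could be adjusted does not make them adjusted: with cohort as the only term they carry the same bias as the simple tests. ANCOVA on a score's own baseline value is not case-mix adjustment, and length of stay, readmission and mortality have no baseline value to use.

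**Conclusion.** The point holds as a fault in what 8.2 fixes: confounders are named only beside the complications model, the secondary analyses open with a univariable commitment, and neither the adjustment of the later models nor the main estimate is stated. It is worth correcting but does not threaten the primary analysis.

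The size rests wholly on assumed inputs. The ranges are 0.06 to 0.15 SD of bias with 7% to 19% false rejection for a continuous outcome, and 0.8 to 5.3 percentage points with 5.4% to 12.3% for the binary example. The upper ends are the worst corners, not expectations.

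A reader might also infer that adjustment is needed to gain power. The protocol does not support that argument: only complications have a planned power, and the usual variance-reduction gain applies to continuous outcomes. The case rests on bias. Adjustment removes only the measured part of it; differences between the two calendar periods that the listed variables do not capture would remain.

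**What to change.** In 8.2, state that:

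1. the planned logistic, survival/competing-risk, ANCOVA and mixed models for the secondary effectiveness endpoints include the listed confounders that are actually collected: age, gender, Katz, Parker, Mini-Cog, Charlson and MNA;
2. the adjusted estimate is the main between-cohort result for each of these endpoints;
3. the univariable tests are descriptive;
4. where events are few, as may be so for in-hospital death, a reduced adjustment is used, for example a single propensity score built from the same covariates.

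The cost is a change of wording and a few more models. No new data are needed and the sample size does not change. The real downside is missing covariates. Under usual care, geriatric assessment happens only on request (3.4), so Mini-Cog, MNA and Parker may be missing more often, and selectively, in retrospective controls. The imputation already planned should cover them, and the amount missing should be reported by cohort.
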